### Additional consent provisions for collection and use of participant data and biological specimens {26b}

No biological specimens will be collected. No additional participant data beyond what is outlined will be utilized.

## Interventions

### Explanation for the choice of comparators {6b}

In the control group, catheters will be removed seven days post-operation as determined by the attending physician. If residual urine volume (RUV) exceeds 100 mL upon catheter removal, this will indicate urinary retention, promoting reinsertion of the catheter. The catheter will be removed on a weekly basis thereafter, until RUV is less than 100 mL [22–24].

### Intervention description {11a}

Health education (preoperative): Prior to the surgery, patients and their family members will be provided with education on IC. This will include an overview of the principles, methodology, and procedural steps of IC, complemented by instructional videos.Supervision and guidance (postoperative days 1–2): Study team members will provide supervision and guidance to patients regarding pelvic floor muscle training (PFMT). Continued education on IC will be delivered through instructional videos to patients and their families.Catheter removal process (postoperative day 3): Following the prescribed fluid intake plan, IDUCs will be removed according to the physician’s instructions. Patients will be encouraged to urinate spontaneously 2–3 times within 2 h of catheter removal. After the last voiding, RUV will be immediately assessed via ultrasound. If RUV exceeds 100 mL, IC will be initiated. The frequency of IC will be adjusted based on RUV. When the frequency of catheterization decreases to once per day and RUV is less than 100 mL after spontaneous urination, bladder voiding function will be considered to be recovered to level II or higher.Patient ability to perform IC will be evaluated by the pencil and paper test [25]. The total score is 15 points, with a score ≥ 9 points indicating patient can perform IC with assistance from medical staff or family. Those scoring < 9 points will require direct assistance from medical staff.Scheduling of IC: The frequency of IC will be tailored according to RUV measurements: 5–6 times daily for RUVs of 350–500 mL (5 times per day: 7:00, 11:00, 15:00, 19:00, 22:00; 6 times per day: 7:00, 11:00, 15:00, 19:00, 22:00, 1:00); 3–4 times daily for RUVs of 200–350 mL (3 times per day: 7:00, 13:00, 19:00; 4 times per day: 7:00, 13:00, 19:00, 22:00); 1–2 times daily for RUVs of 100–200 mL (once per day at 19:00; twice per day at 7:00 and 19:00). Specific timing for catheterization is outlined.Drinking plan: Total daily fluid intake is set 1500–2000 mL, and not exceed 2500 mL [12, 13]. Drink 400–500 mL of each meal (including intravenous infusion, liquid beverages, milk, soup). Between meals, patients may drink 200–300 mL of fluids every time. Fluids should be avoided from 20:00 to 6:00.Voiding diary for IC: Participants will record intake amounts (including intravenous infusion volume during hospitalization), spontaneous voided volume, urination times, IC interval, catheterized volume, uresiesthesia and symptoms over a continuous 24-h period. Milliliter was used for fluid unit. And fluid volume was determined by professional tools.Bladder training: Exception pelvic floor rehabilitation training, patients undergoing IC will participate in bladder training, which includes scheduled urination, urge suppression, and compensatory voiding maneuvers to enhance urinary behavior.

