### Trial design {8}

This study is a parallel-group superiority randomized controlled trail conducted at a single center, with an allocation ratio of 1:1. We hypothesize that early urinary catheter removal combined with IC is superior in terms of efficiency and effectiveness compared to IDUCs. All participants in the study will be assessed weekly and followed for 3 months. The flow chart is shown detailing the study design, and all interventions and outcome measures are presented in Fig. 1 and Table 1 respectively. This trial follows the report standard of SPIRIT 2013.

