### Sample size {14}

Based on the bladder function recovery rate at 2 weeks post-surgery (Bladder Function Recovery Grade II or higher) observed in pretest, the sample size was determined. The recovery rate for the IC group was 78.95%, compared to 38.89% IDUCs group. Using a unilateral *α* of 0.025, a desired power of 0.9 (i.e., 1 − *β* = 0.9) and the margin of 5%, the sample size was calculated using the following formula.$$n=\frac{{2\overline{p }\overline{q }\left({z}_{\alpha }+{z}_{\beta }\right)}^{2}}{{\left({p}_{1}-{p}_{2}\right)}^{2}}$$

Based on these parameters, the calculated sample size for each group was determined to be 35 cases. To facilitate 1:1 randomization, a total of 70 cases would be required. However, anticipating potential loss due to follow-up dropouts and refusal of participation (estimated at 10–15%), the final minimum number of research subjects for each group was determined to be 39 cases. Therefore, at least 78 participants are deemed necessary to ensure sufficient statistical power for this study.

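### The protocol describes residual urine volume and recovery differently by arm and fixes no common week-2 measurement for the primary endpoint

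*Protocol article*

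**What the plan says.** **Intervention arm** (Intervention description {11a}). On postoperative day 3 the catheter is removed in line with a fluid plan. Then: "Patients will be encouraged to urinate spontaneously 2–3 times within 2 h of catheter removal". Ultrasound follows at once after the last void, and a reading above 100 mL starts intermittent catheterization (IC). The same section gives a recovery rule for this arm: once IC is down to one catheterization a day and RUV after a spontaneous void is under 100 mL, the patient counts as level II or better. The drinking plan stands in this section too: "Total daily fluid intake is set 1500–2000 mL, and not exceed 2500 mL", with no fluids between 20:00 and 6:00.

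**Control arm** (Explanation for the choice of comparators {6b}). The catheter comes out on day 7. "If residual urine volume (RUV) exceeds 100 mL upon catheter removal, this will indicate urinary retention", and it is then reinserted and removed weekly until RUV is under 100 mL. Number of voids, interval, method and fluid conditions are not given.

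**Primary outcome** (Outcomes {12}). Recovery at 2 weeks is an RUV under 100 mL after a spontaneous void, in the same words for both arms. Grades I and II also require bladder fullness sensation and desire to void. No voided-volume or filling condition is set, and no week-2 measuring procedure is described.

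**The concern.** RUV depends on how it is taken. It falls with each further void and rises with bladder filling. An absolute cut of 100 mL gives the same answer in two groups only if both are tested under the same conditions.

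Here one arm has a detailed test and its own recovery rule. The other has a single phrase tied to catheter removal. Participants and staff know the allocation. If each arm's section is followed as written, the two arms reach the primary endpoint by different routes, and part of the observed difference may come from the test and not from the treatment.

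**Working it through.** **1. The two routes to the week-2 endpoint**

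| Item | Intervention {11a} | Control {6b} | Primary outcome {12} |
|---|---|---|---|
| Time | Day 3, then during IC | Day 7, then weekly | 2 weeks |
| Voids before reading | 2–3 in 2 h (day 3) | Not given | A spontaneous void; number not given |
| Method | Ultrasound | Not given | Not given |
| Fluid conditions | Drinking plan | Not given | Not given |
| Recovery rule | IC once daily and RUV < 100 mL | RUV < 100 mL | RUV < 100 mL, with sensation in the grades |

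A control who fails on day 7 is next tested on day 14, from a bladder just drained by catheter. An intervention patient at week 2 has had no indwelling catheter since day 3. A day-3 or IC-based pass might stand as the week-2 result or might be re-measured; the text does not say.

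**2. Why test conditions matter for a 100 mL cut**

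Inputs: the intake in {11a}; output taken as equal to intake, a principle the Discussion invokes; and a bladder empty at catheter removal (assumption). Volume formed in 2 h = daily intake × 2 / hours.

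- Over 24 h: 1500 × 2/24 = 125 mL and 2000 × 2/24 = 167 mL. Voiding 25 mL (25/125 = 20%) or 67 mL (67/167 = 40%) leaves 100 mL.
- Over the 14 permitted drinking hours: 1500 × 2/14 = 214 mL and 2000 × 2/14 = 286 mL. Now 114 mL (53%) or 186 mL (65%) must be voided.

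The low-filling effect is therefore strong under the first assumption and weak under the second.

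Repeat voids, assuming 40% emptying each time and no refill, so RUV = start × 0.6^k:

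- From 200 mL: 120 mL after one void, 72 after two, 43 after three. The number of voids decides the result.
- From 150 mL: 90 mL after one void. The reading passes at once, so the number of voids is irrelevant to the cut.

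Low filling and repeat voiding are thus alternative mechanisms, and their effects should not be added together.

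**3. The plan's sample size**

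Inputs from Sample size {14}: "The recovery rate for the IC group was 78.95%, compared to 38.89% IDUCs group"; "Using a unilateral *α* of 0.025"; "a desired power of 0.9"; and "the margin of 5" (per cent). Trial design {8} adds "with an allocation ratio of 1:1".

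With unpooled variance and the margin subtracted:

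n = (0.7895 × 0.2105 + 0.3889 × 0.6111) × (1.960 + 1.282)² / (0.4006 − 0.05)² = 34.5, so 35 per group, as stated.

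The printed pooled formula without the margin gives 31.7, so 32. This does not affect the present point.

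**4. What misreading could do at 35 per group (illustration)**

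Let m be an assumed share of truly non-recovered patients who read below 100 mL. The apparent rate is p + m(1 − p). The probability of a significant result in favour of IC is Φ[(d − 1.96·se0)/se1], where d is the apparent difference, se0 uses the pooled rate and se1 the separate rates, for a test of zero difference.

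Example: m = 20% in the intervention arm only, true rate 38.89% in both. Apparent rates are 0.5111 and 0.3889, d = 0.1222, se0 = 0.1189, se1 = 0.1180. Then Φ[(0.1222 − 0.2331)/0.1180] = Φ(−0.939) = 0.174.

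| m | Intervention only, no true effect: chance of significance | Both arms, planned rates: difference (points), power | Control only, planned rates: difference (points), power |
|---|---|---|---|
| 0 | 0.025 | 40.1, 0.943 | 40.1, 0.943 |
| 10% | 0.074 | 36.1, 0.895 | 33.9, 0.849 |
| 20% | 0.174 | 32.0, 0.829 | 27.8, 0.693 |
| 30% | 0.333 | 28.0, 0.747 | 21.7, 0.496 |

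No value of m can be taken from the protocol. The table shows only that the conclusion is sensitive in either direction.

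**The case against.** The strongest reply concerns the time point. The 2–3 voids belong to the day-3 test that decides whether IC starts, while the primary outcome is measured at 2 weeks and worded alike for both arms. A reader might infer that intervention patients are read after repeat voids at week 2 and controls are not. The text does not say so. Control conditions are unstated, not stated to differ, and a condensed article may leave the number of voids or the scan delay to the full protocol.

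A reader might also infer that the bias favours the intervention, or that the same bladder would pass in one arm and fail in the other. Neither is established. At week 2 it may be controls who are tested from a freshly drained bladder, and low filling would then help them. The sensation criteria in Grades I and II partly guard against a low RUV alone counting as recovery, and a blinded evaluator assesses outcomes that are not self-reported. The 100 mL cut itself comes from a cited grading.

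All of this stands and limits the claim. It does not remove it. Blinding does not equalise the conditions under which a reading is obtained. The recovery rule in {11a} uses the endpoint's own terms, omits sensation and has no counterpart in {6b}. The difficulty is therefore more than omitted detail: the article gives arm-specific routes to the primary endpoint and does not say which governs at week 2.

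**Conclusion.** The point holds in a limited form. The documents describe RUV and recovery differently by arm and fix no common week-2 measurement, so the primary comparison can mix test conditions with treatment effect. Direction and size cannot be derived. The figures above rest on assumed filling, emptying fractions and misreading shares, and show sensitivity only. The stated sample size of 35 per group is unaffected. This should be corrected because the measurement defines the primary endpoint and the correction is cheap; it is not evidence that the trial is biased towards IC.

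**What to change.** For the week-2 primary measurement only:

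- Write one RUV test for both arms: same fluid instruction beforehand, same number of voids, same delay to the scan, ultrasound in both, read by the blinded evaluator.
- Apply the grade in Outcomes {12} identically in both arms, including the sensation criteria, and state whether an earlier pass can stand as the week-2 result.
- Record voided volume with RUV in everyone, so that a sensitivity analysis can use voided plus residual volume.
- Reconcile {6b}, {11a} and {12} on how RUV and recovery are determined. The clinical triggers for IC and for catheter reinsertion stay with the sponsor.

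A minimum bladder volume for accepting a reading is optional, since it would modify the cited grading.

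Cost: protocol and case report form wording, one extra voided-volume measurement in controls (the IC diary already records it in the intervention arm), and slightly longer visits. Recruitment began in September 2022, so patients measured before the change should be identifiable in the analysis.

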
### Criteria for discontinuing or modifying allocated interventions {11b}

Patients may switch intervention options or withdraw from this study at their discretion. If a patient decides to withdraw, efforts will be made to finalize and document their data beforehand. The reasons and timing of patient withdrawal will be detailed in the case report. If patients opt out of the trial, their study participation may be terminated.

### Strategies to improve adherence to interventions {11c}

A team member will be assigned to manage each participant’s follow-up through WeChat APP or telephone post-discharge. And participants will submit their “IC Voiding Diary (intervention group)” and “Indwelling Catheter Care Record (control group)” to research team, enhancing adherence significantly.

### Relevant concomitant care permitted or prohibited during the trial {11d}

All participants enrolled in the study will receive essential baseline care throughout the study, including pelvic floor rehabilitation training starting 6 h post-operation and continue for up to 3 months [26].

### Provisions for post-trial care {30}

The trial does not increase risks beyond what may result from routine management. All patients will receive routine postoperative care independent their allocation.

### Outcomes {12}

#### Primary outcomes

The primary outcome measure for this study is the rate of bladder function recovery (Bladder Function Recovery Grade II or higher) 2 weeks post-surgery. Bladder function recovery is quantified by a RUV less than 100 mL following spontaneous urination after catheter removal. The grading system for bladder function recovery is as follows [27]: Grade I: Patient has a bladder fullness sensation and urination desire, can urinate spontaneously upon catheter removal, and has a RUV of less than 50 mL, indicating effective bladder function recovery; Grade II: Patient has a bladder fullness sensation and the desire to urination, can urinate spontaneously upon catheter removal, but the RUV is between 50 and 100 mL, suggesting slightly diminished bladder function recovery. Grade III: Patient lacks bladder fullness sensation or urination desire, can urinate spontaneously upon catheter removal, but RUV exceeds 100 mL, reflecting poor bladder function recovery; Grade IV: Patient has no sensation of spontaneous urination and cannot urinate independently with various interventions after catheter removal, indicating lack of bladder function recovery.

#### Secondary outcomes

Urinary tract infection within the first month post-surgery [28]. Patients have symptoms, including urinary urgency, frequency, pain, or other urinary irritation symptoms, as well as lower abdominal tenderness, flank tenderness, and potentially with or without fever. Diagnosis is confirmed by finding white blood cells ≥ 10/ high power field in urine examinations, coupled with urine cultures in catheterized patients.Bladder dysfunction within three months post-surgery: Assessed using the Mesure Du Handicap Urinaire (MHU) bladder function scale for self-assessment.Changes in urodynamic parameters within 1 month post-surgery: This involves comparing urodynamic measurements, including maximum flow rate, average flow rate, RUV, bladder safe capacity, maximum detrusor pressure, and bladder compliance.

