**Methods:**

Cervical cancer patients undergoing laparoscopic radical hysterectomy will be recruited to this randomized controlled trial. Participants will be randomly assigned to either early postoperative catheter removal combined with intermittent catheterization group or a control group receiving standard care with indwelling urinary catheters. All these patients will be followed for 3 months after surgery. The study’s primary endpoint is the comparison of bladder function recovery rates (defined as achieving a Bladder Function Recovery Grade of II or higher) 2 weeks post-surgery. Secondary endpoints include the incidence of urinary tract infections, and changes in urodynamic parameters, and Mesure Du Handicap Urinaire scores within 1 month postoperatively. All analysis will adhere to the intention-to-treat principle.

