## Data collection and management

### Plans for assessment and collection of outcomes {18a}

Outcome assessments will be meticulously documented by the research evaluator on the case report form (CRF), identifying participants by their study ID numbers and initials, thus ensuring confidentiality. Baseline assessments will be conducted prior to surgery. Evaluations for postoperative urinary tract infection are scheduled at 3 days, 1 week, 2 weeks, 3 weeks, and 4 weeks post-surgery. Assessments for bladder dysfunction post-operation will occur at 1 week, 2 weeks, 3 weeks, 1 month, and 3 months post-surgery. Urodynamic results will be collected 1 month post-surgery. Follow-up will be conducted through WeChat APP or telephone.

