## Statistical methods

### Statistical methods for primary and secondary outcomes {20a}

An intention-to-treat analysis will be performed, utilizing the last available measurement for instance of data lost. The collected data was analyzed using SPSS 20.0 software. Continuity data will undergo normality testing; those with a normal distribution will be analyzed using an independent sample *t* test, while those with a skewed distribution will be assessed using non-parametric test. Chi-square test was used for enumeration data, mean value ± standard deviation ( $$\overline{x }$$±S) for measurement data. When *p* < 0.05, the difference can be considered statistically significant.

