### Methods in analysis to handle protocol non-adherence and any statistical methods to handle missing data {20c}

The intention-to-treat analysis will be used in this study. Missing objective data will be interpolated with mean values, and the missing subjective data will not be interpolated. The effectiveness of these methods for handling missing data will be assessed through sensitivity analysis. Further, to evaluate the impact of non-adherence on study outcomes, the per-protocol analysis will also be adopted.

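### The MHU symptom endpoint has two windows (1 month and 3 months), no named main visit and two conflicting missing-data rules, and its earliest visits overlap control-arm catheterisation

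*Protocol article*

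**What the plan says.** All references are to the protocol article.

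- Outcomes {12}, Secondary outcomes: "Bladder dysfunction within three months post-surgery: Assessed using the Mesure Du Handicap Urinaire (MHU) bladder function scale for self-assessment".
- Abstract, Methods, listing the secondary endpoints: "Mesure Du Handicap Urinaire scores within 1 month postoperatively".
- Section {18a}: "Assessments for bladder dysfunction post-operation will occur at 1 week, 2 weeks, 3 weeks, 1 month, and 3 months post-surgery". The outcomes section measures bladder dysfunction by the MHU, so this is the MHU schedule. No visit is singled out.
- Section {6b}, on controls: "catheters will be removed seven days post-operation", with reinsertion if residual urine volume (RUV) is above 100 mL. Then: "The catheter will be removed on a weekly basis thereafter, until RUV is less than 100 mL".
- Section {14}, on recovery at two weeks in the pretest: "The recovery rate for the IC group was 78.95%, compared to 38.89% IDUCs group".
- Section {20a}, headed as covering primary and secondary outcomes: "Continuity data will undergo normality testing", followed by a two-sample t test or a non-parametric test. The same section replaces lost data with the most recent recorded value and makes no exception for self-reported data.
- Section {20c}: "the missing subjective data will not be interpolated". It adds that the missing-data methods will be examined in a sensitivity analysis.

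**The concern.** The background section says that earlier studies did not assess subjective symptoms of bladder dysfunction. The MHU is the trial's self-report instrument for that gap. Section {17a} limits blinded assessment to outcomes that are not self-reported, so patients who know their allocation supply the score. An outcome in that position needs a fixed time point before data are seen. Here one place would end the comparison at 1 month and another at 3 months.

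The two windows compare different things. In the first two weeks most controls are on continuous drainage or have just come off it, while the other arm attempts voiding from day 3. At 3 months the scheduled catheter period is furthest away. A 1-month window also leaves out the only visit beyond the first month.

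The missing-data rules add a second ambiguity. Function is expected to improve over time, so carrying an early score forward understates later recovery. If the MHU is taken before surgery, a carried preoperative score would overstate function after it. Leaving the score missing gives a third result. Two analysts following the text could report different MHU results from the same data.

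**Working it through.** **1. Windows side by side.**

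| Place | Window or visits |
|---|---|
| Abstract | 1 month |
| Secondary outcomes | 3 months |
| Section {18a} | weeks 1, 2, 3, month 1, month 3 |
| Trial design {8} | follow-up to 3 months |

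Three places agree on 3 months and the abstract does not. None names a main visit.

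**2. Controls at the early visits.** The plan states no figure for the MHU. The inputs are its group size and pretest rates.

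- Group size: 35 / (1 − 0.10) = 38.9, so 39 per arm, as section {14} states.
- Controls unrecovered at week 2: 1 − 0.3889 = 0.6111; 0.6111 × 39 = 23.8, about 24.
- Intermittent catheterization arm unrecovered: 1 − 0.7895 = 0.2105; 0.2105 × 39 = 8.2, about 8.
- Week 1: all controls are scheduled to be catheterised up to day 7.
- Week 2: if recovery is not lost once gained, the 61% unrecovered at day 14 had also failed at day 7. They had the catheter back between days 7 and 14.
- Week 3 and later: no recovery rate is given, so no share can be computed.

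**3. Missing-data rules for one missing MHU score.** Under {20a} the previous score is used. Under {20c} nothing is used. Both cannot hold. The sensitivity analysis promised in {20c} does not say which rule is primary.

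**4. Illustration only: if unrecovered controls gave no usable week-2 score.** Usable controls would be 0.3889 × 39 = 15.2, about 15. The detectable difference in SD units at 80% power, two-sided 5%, is (1.960 + 0.842) × √(1/n₁ + 1/n₂).

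- 39 v 39: 2.802 × 0.2265 = 0.63 SD.
- 39 v 15: 2.802 × 0.3038 = 0.85 SD.

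**5. Illustration only: if each of five visits were tested at 5%.** With independent visits, 1 − 0.95⁵ = 22.6%. By simulation with an assumed between-visit correlation of 0.3, 0.5 or 0.7, the chance of at least one false positive is about 21%, 18% or 15%.

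Steps 4 and 5 rest on conditions that the document does not state.

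**The case against.** The window conflict is confined to a condensed abstract. The outcomes section, schedule and follow-up agree, so a wording correction settles it. That stands for the window, but it does not supply the missing main visit or the missing-data rule.

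Repeated-measures handling, multiplicity and covariate adjustment are commonly left to an analysis plan, which is not shown. That also stands: their absence is no finding here. What remains is what the article does state, namely a normality-gated two-sample test for five repeated scores and two incompatible rules.

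A reader might infer three stronger claims, and the document supports none of them.

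- *Early comparisons keep only the best-recovered controls and so are biased against intermittent catheterization.* Nothing says that catheterised patients skip the MHU or are set to missing, and the items are not given. Unrecovered patients in the other arm are catheterised too, intermittently, so early comparability is a question for both arms.
- *Each visit gets its own test, so the false-positive rate is 15–18%.* Section {20a} does not say that each visit is tested.
- *Baseline is ignored at a known cost in precision.* Section {18a} has preoperative assessments but does not say that the MHU is among them. The table of measurements is not shown, and no correlation is given.

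It is also fair to say that the control visits at weeks 1, 2 and 3 coincide with scheduled removal attempts. A score may therefore be taken just after removal. This makes it more important to record catheter status.

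**Conclusion.** The endpoint definition is inconsistent, and the point holds in that form. The MHU has two windows, five visits without a main one, and two missing-data rules that cannot both apply. The consequence is not trivial: about 61% of controls (24 of 39) are expected to be unrecovered at week 2, so scores at weeks 1 and 2 largely describe catheter status. That figure rests on the pretest rate applying in the trial. The statement about days 7 to 14 also assumes that recovery is not lost once gained.

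No direction of bias, false-positive rate or precision gain is established. The detectable differences and error rates above are illustrations under assumed conditions. This is a secondary endpoint and the primary outcome is unaffected. The correction is still worth making, because this is the outcome on which the trial's claim about subjective symptoms depends.

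**What to change.** Make these changes in the analysis plan, and in a correction to the article's wording, before MHU data are compared between arms:

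1. Change the abstract's MHU window to match the outcomes section.
2. Name MHU at 3 months as the main MHU comparison, with the earlier visits supportive.
3. Replace the normality-gated t or rank test for this outcome with a mixed model over the scheduled visits. Report the 3-month contrast, adjusted for preoperative MHU if it is collected, with a rank or bootstrap analysis as a check.
4. Replace the two missing-data rules with one for the MHU: likelihood-based handling within that model (valid if scores are missing at random) and no last value carried forward.
5. Record catheter status at each MHU visit and report it beside the early scores in both arms. Do not give catheterised patients a worst score. An indwelling catheter is the control arm's assigned care, so that rule would penalise controls for their allocation and favour the other arm.

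The cost is wording, a standard model and one extra recorded item. The small downside is that early MHU results become supportive.

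### Mean substitution for missing objective data makes no exception for patients who cannot void, so a blank maximum or average flow rate at 1 month would be scored as average

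*Protocol article*

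**What the plan says.** Under Secondary outcomes, the protocol article lists "Changes in urodynamic parameters within 1 month post-surgery" and describes this as "comparing urodynamic measurements, including maximum flow rate, average flow rate, RUV, bladder safe capacity, maximum detrusor pressure, and bladder compliance". Section {18a} gives one time for the measurement: "Urodynamic results will be collected 1 month post-surgery". It also says "Baseline assessments will be conducted prior to surgery", but the readable text does not say whether those include urodynamics, and Table 1 is not shown.

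The grading scale under Primary outcomes foresees patients who do not void. A Grade IV patient "cannot urinate independently with various interventions after catheter removal". Grade III is different: that patient voids spontaneously but leaves more than 100 mL behind.

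Two general rules cover missing values. Statistical methods {20a} uses the last available measurement where data are lost. Section {20c} says: "Missing objective data will be interpolated with mean values". Section {20c} also promises a sensitivity analysis, without giving its content. Neither rule separates a patient who could not void from a test that was not done, and no sentence says what flow value a non-voider receives.

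**The concern.** A flow rate needs a void. For a patient who attends the 1-month test and passes no urine, the absence of a flow reading is the treatment result, and the worst one on that scale. The two arms may also differ in how many such patients they have.

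Flow rate is objective data. If the reading is left blank, section {20c} read literally replaces it with a mean that can come only from patients who did void. The failed bladder is then counted as an average one. If early removal with intermittent catheterization (IC) leaves fewer non-voiders, that part of the benefit drops out of the two flow comparisons. If it leaves more, that part of the harm drops out.

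Settling which of the two missing-data rules applies would not cure this, because neither recognizes inability to void as an outcome.

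**Working it through.** **Plan's own figure.** The protocol gives none for flow rate, for the share unable to void at 1 month, or for power on the urodynamic measures. The only figure used from it is 39 per arm (Sample size {14}: 35 / (1 − 0.10) = 38.9, rounded up to 39).

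**What the protocol says about numbers.** The pretest recovery rates at 2 weeks are 78.95% (IC) and 38.89% (indwelling catheter). Unrecovered patients would number 39 × (1 − 0.7895) = 8.2 and 39 × (1 − 0.3889) = 23.8. These counts include Grade III patients, who do void, and refer to 2 weeks rather than 1 month. They are at most a loose upper guide to non-voiders.

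**Assumptions, none from the documents.** Flow among voiders averages m = 15 mL/s (SD 6) in both arms. The share unable to void is q_IC or q_C. Blanks are filled with the pooled mean of voiders.

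**Formulas.**
- Non-voiders scored 0: arm mean = (1 − q) × m + q × 0 = m(1 − q), so the difference (IC minus control) = m(q_C − q_IC).
- Pooled-mean substitution: arm mean = (1 − q) × m + q × m = m in each arm, so the difference = 0.

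Gaps of 8, 15 and 25 points give 15 × 0.08 = 1.20, 15 × 0.15 = 2.25 and 15 × 0.25 = 3.75 mL/s.

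**Simulation.** 4,000 trials of 39 per arm, two-sided 5% level. Scoring 0 is paired with a Mann-Whitney test, pooled-mean substitution with a t test.

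| Non-voiders, IC v control | m × gap | Difference, scored 0 | Difference, mean substituted | Rejection, scored 0 | Rejection, mean substituted |
|---|---|---|---|---|---|
| 0% v 0% | 0 | 0.01 | 0.01 | 4.4% | 4.6% |
| 2% v 10% | 1.20 | 1.18 | −0.02 | 8.2% | 5.1% |
| 5% v 15% | 1.50 | 1.52 | 0.01 | 11.5% | 4.7% |
| 5% v 20% | 2.25 | 2.28 | 0.03 | 21.2% | 5.1% |
| 5% v 25% | 3.00 | 3.02 | 0.00 | 33.0% | 4.9% |
| 10% v 30% | 3.00 | 3.05 | 0.02 | 34.6% | 5.2% |
| 5% v 30% | 3.75 | 3.77 | −0.02 | 49.0% | 4.6% |

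Flow among voiders was floored at 2 mL/s in the 5% v 20% and 5% v 30% rows and at 1 mL/s in the others. This explains the slight excess over m × gap in several rows.

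**Last-value rule.** Carrying a value forward needs an earlier urodynamic reading. The word for change in the outcome hints at a preoperative one, but the readable text does not confirm it, so this route was not computed.

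**The case against.** The strongest reply is that nothing in the protocol says a non-void is recorded as missing. The evaluator could enter 0 mL/s, and then neither rule applies. That stands, and it makes the point conditional. But the protocol does not say this either, and the rule in {20c} is stated without exception.

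A second reply is that coding a failed void belongs in the case report form or analysis plan. As a bare omission it would. Here, however, the protocol itself states a substitution rule that gives a wrong value when applied to a case its own grading scale foresees. The unspecified sensitivity analysis does not alter the main handling.

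Third, the illustration has its result built in. With equal flow among voiders, substitution must return about 0. This is fair: the table shows the mechanism and its scale under stated assumptions, and does not estimate the bias in this trial. With a 2% v 10% split the gain in rejection is small (5.1% to 8.2%).

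Three stronger readings are tempting and are not supported:
- A reader might infer that every control with residual urine above 100 mL lacks a flow value, because "The catheter will be removed on a weekly basis thereafter, until RUV is less than 100 mL" sets no end date. Grade III patients in that range void spontaneously, and the weekly removals allow voiding to be tried. Only patients unable to void at all are affected.
- A reader might infer that such patients will receive an earlier, better flow value. That needs an earlier measurement which the readable text does not establish.
- A reader might infer that the trial hides its worst outcomes. It does not. Grade IV counts as not recovered in the primary endpoint, and residual urine volume and the self-assessed bladder scale are compared as well.

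**Conclusion.** The point holds in conditional form, for two secondary measures. If a flow value is left blank because the patient could not void, section {20c} assigns it a mean and biases the maximum and average flow comparisons toward no difference. The last-value rule in {20a} would do similar damage only if an earlier urodynamic measurement exists.

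The true size is unknown, because the documents give neither the 1-month non-voiding rate nor any flow values. Under the assumptions above, a gap of 8 to 25 points in non-voiding corresponds to about 1.2 to 3.8 mL/s, all of which disappears under pooled-mean substitution. The primary endpoint is unaffected. The change is worth making before the data are locked, because it is cheap and the present rule has no safeguard.

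**What to change.** In Secondary outcomes and in section {20c}, state that inability to void at the 1-month test is an outcome. It is recorded as 0 mL/s, the worst rank, for maximum and average flow rate, and is exempt from mean or last-value substitution. If the analysis uses change from baseline, assign the worst rank to the change directly, since 0 minus a low baseline need not be the lowest value. Keep imputation only for tests that were not done.

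Name the non-parametric test, which {20a} already allows for skewed data, as the comparison for these two parameters, and report the number unable to void in each arm.

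The cost is a few sentences and no new data. The small downside is that the result becomes a rank comparison rather than a difference in means.
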